#### Cognitive behavior therapy (CBT)

CBT was selected as the non-pharmacological treatment for this study because of its well-documented clinical efficacy in depressed patients at all levels of depression severity and chronicity
[12]. It offers specific advantages over other psychotherapies for a study of this type. Specifically, the therapeutic process has been validated and the general goals and procedures for each session are standardized with available published training manuals
[73]. Training and competence measures can be evaluated to insure a consistent standard of care for all patients.

The CBT package employed in the PReDICT study utilizes a standardized treatment protocol
[73]. CBT pursues symptomatic relief from depression through a systematic effort to change depressed patients’ automatic and maladaptive ways of thinking. At the heart of this approach is the assumption that distorted views about the self, the world, and the future maintain depressive affect. Patients first work at becoming aware of these thinking styles, and then learn ways of thinking differently so that their cognitive processes become more adaptive. These skills, when accompanied by affective arousal and practiced in the context of extra homework assignments, are an important engine of symptom resolution
[74]. Patients are first asked to record or keep track of their thoughts, especially those accessed in the midst of problematic emotional situations. During the course of treatment, the therapist gradually moves the focus of therapy from these distorted cognitions about themselves, the world, and the future to identification and modification of the underlying depressogenic maladaptive cognitive processes or errors. Finally, the patient comes to understand the beliefs underlying the cognitive processes and self-statements, and the therapy focuses on helping the patient change the underlying erroneous beliefs.

The typical course of CBT comprises 12 to 20 1-h sessions; in this study, 16 sessions are provided. The sequence of therapy involves three stages. In the early stage (sessions 1 to 4) the emphasis is on establishing a therapeutic relationship with the patient, educating the patient about the cognitive model and emotional lability, setting goals, and identifying, eliciting, and evaluating automatic thoughts. The middle phase (sessions 5 to 12) involves a gradual shift towards the identification of dysfunctional beliefs and compensatory strategies the patient may be employing, helping the patient to: (1) identify dysfunctional cognitive processes (for example, overgeneralization, mind reading) and core beliefs or schema; and (2) practice skills at responding to and modifying depressogenic processes and schema. Tasks in the late stage of CBT (sessions 13 to 16) revolve around preparing the patient for termination, predicting high-risk situations relevant to relapse, and consolidation of learning self-therapy tasks. To complete the 16 visits during the 12 weeks of intervention, patients randomized to CBT see their therapist twice per week for the first 4 weeks and then weekly for the remaining 8 weeks. The number of sessions attended is tracked for each patient.

Doctoral-level and masters-level providers trained in the specific CBT protocol for the study will provide the therapy. Patients who complete at least 12 sessions of CBT will be considered to have completed the course of CBT. All CBT-treated patients continuing in the study after week 12 receive three booster sessions at monthly intervals over the first 3 months and another three booster sessions, each separated by at least 1 month, during the second year of follow-up. There is also one additional crisis session available to patients during each year of follow-up. All therapy sessions are videotaped, and an independent off-site CBT expert at Beck’s Institute of Cognitive Therapy rates selected sessions of all therapists’ competence in Beck’s type of CBT
[73].

#### Acute monotherapy phase assessment visits

All patients are seen for symptom severity ratings visits weekly for the first 6 weeks and bi-weekly for the remaining 6 weeks of the acute phase. At each visit, the patient completes the BDI and QIDS, and undergoes assessment with the HDRS, MADRS, and HARS with a blinded rater. All patients also meet with a study psychiatrist for assessment of CGIs, concomitant medications, adverse events, and safety. Thus, all patients, regardless of treatment assignment, meet with a study psychiatrist at all ratings visits throughout the study. Ratings visits are scheduled to coincide with a treatment visit (whether CBT or medication) to minimize patient time demands.

For patients randomized to medication, the study psychiatrist also assesses medication compliance, response to treatment, and need for dose adjustment at each of the ratings visits. For all patients, the psychiatrist limits the visit to a maximum of 20 min, unless an urgent clinical situation requires greater intervention. The total time the psychiatrist spends with the patient at each visit is recorded, and psychiatrists are instructed to adhere to the *Clinical Management Manual* developed by Fawcett *et al*.
[75].

Patients who do not remit (that is, those with an HDRS-17 total score of ≥8 at either week 10 or week 12) following 12 weeks of monotherapy are offered the option to enter an additional 12-week course of combination treatment. Patients who initially received a medication as monotherapy continue on that medication in a double-blind manner, and begin the 16-session course of CBT. Patients who initially received CBT will have open-label escitalopram added to their treatment, following the same dosing guidance as described for the monotherapy treatment. We chose to use open-label medication in this phase due to inadequate power to identify differences between randomized treatments. These patients also meet with their CBT therapist once per month for a total of three monthly booster sessions over this 12-week period. The visit structure for this combination phase treatment replicates that of the monotherapy phase: weekly ratings visits for 6 weeks, followed by bi-weekly ratings visits for the next 6 weeks. At the end of this 12-week combination treatment period (that is, week 24 from baseline), patients are assessed for response to the combination treatment (see below). Those who remit or respond (defined below) can continue into the long-term follow-up phase (described below) for an additional 18 months, following the same visit schedule as the monotherapy phase remitters.

#### Long-term follow-up visits

Patients who are remitters at the end of the acute phase, or who are remitters or responders at the end of combination treatment are eligible to enter into long-term follow-up. These patients return for an assessment at the end of each 3-month period following the end of their acute treatment (that is, week 12 for monotherapy remitters, week 24 for remitters/responders to combination treatment). The assessments at these follow-up visits consist of a Longitudinal Interval Follow-up Evaluation (LIFE) interview
[76], a clinical interview by a psychiatrist, clinical ratings on the HDRS, MADRS, and HARS by a trained blinded rater, and self-report measures. Patients continue in the follow-up phase until: (1) 2 years from study baseline; or (2) depressive recurrence (defined below). If, between scheduled follow-up phase visits, the patient reports clinically important return of symptoms and functional impairment such that they desire additional or alternative antidepressant treatment, they are considered to be at risk for recurrence, and a LIFE will be conducted as soon as possible.

#### Major endpoints

##### Remission

Remission, the study’s primary outcome measure, is defined as a HDRS-17 item total score <8 at both the week 10 and week 12 ratings visits for patients in the acute monotherapy phase. For patients who enter the combination treatment phase, remission is defined as a HDRS-17 item total score <8 at both the week 22 and week 24 ratings visits. Remitters from either the monotherapy or combination treatment phases are eligible to enter the long-term follow-up phase (21 months for monotherapy remitters; 18 months for combination remitters), returning every 3 months for assessments or until depression recurrence.

##### Response

Response is defined as ≥50% reduction from the baseline HDRS-17 item total score, and response will be used as a secondary outcome measure. Response is determined based on the HDRS-17 item rating at the week 12 and week 24 visits. For the non-remitters at week 12, the week 24 response/non-response status is used to determine further study participation. Responders at week 24 (that is, those patients who did not remit during the initial 12-week monotherapy phase, but who meet criteria for response at the end of the combination treatment phase) are offered the option to enter into the long-term follow-up phase. These patients return every 3 months for assessments for 18 months, or until depression recurrence, following the same follow-up schedule as the remitting patients. Recurrence is defined as the occurrence of any one of the following four criteria during the long-term follow-up phase: (1) Meeting full criteria for a major depressive episode: determined through a LIFE score of 3 for major depression, administered by a blind rater; (2) A 17-item HDRS ≥14 score in 2 consecutive weeks: blinded raters will administer the HDRS at the scheduled follow-up visits. A patient scoring ≥14 at a follow-up visit will be asked to return the subsequent week for a repeat rating. If that rating is also ≥14, the patient is considered to have had a recurrence; (3) A 17-item HDRS score ≥14 at any follow-up visit, and at which the patient requests an immediate change in treatment for their depressive symptoms; and (4) High current risk for suicidality (as assessed by the study psychiatrist) that warrants urgent intervention.

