[12,13]. Despite these advances, depression treatment continues to be hampered by two major limitations: an unacceptably low rate of symptomatic remission, and the virtual absence of any practical predictors of treatment response, whether partial or complete. Although it is widely considered that current interventions benefit approximately 60% of MDD patients, only about 30% to 40% of patients show full remission of their symptoms as defined by the MacArthur criteria (for example, a 17-item Hamilton Depression Rating Scale (HDRS) score <8)
[14,15]. Approximately 30% more demonstrate some response to treatment, indicating they experience clinically important reductions in their depressive symptom burden, yet also continue to experience clinically important residual symptoms. Patients who experience a response short of remission are more vulnerable to relapses and recurrences of the disorder
[16] and experience greater functional disability
[17].

Current treatment for MDD involves a trial-and-error approach because there are no consistently identified predictors of differential response across treatment modalities. Primary first-line treatments consist of either an evidence-based form of psychotherapy or antidepressant medication. In patients treated pharmacologically, several treatment options are available, but there are very few clinical trial data to guide clinicians as to which first step enhances the odds of remission for an individual patient
[18]. Illustrating the importance of such trials, one retrospective study found a differential advantage for psychotherapy over medication (nefazodone) in chronically depressed patients with early life trauma
[19]. A treatment regimen that ultimately proves to be ineffective results in continuing patient distress and role dysfunction, discouragement regarding possible relief from MDD, exposure to potential side effects, and unnecessary medical costs. Among the roughly 70% of depressed patients who do not remit with their first treatment, many do not return to explore other treatment options that might have proven effective
[20].

Previous efforts attempting to identify predictors of treatment response have typically been *post-hoc* analyses of datasets designed to test other hypotheses

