### Aims

The primary aim of PReDICT is to identify predictors of remission with acute treatment for MDD; predictors comprise genetic, endocrine, immune, and personality measures, as well as baseline and early-treatment fMRI of the central nervous system. Predictors will be identified by utilizing sophisticated multivariate procedures to determine which variables have clinically important and statistically significant effects for the prediction of remission and response.

A secondary aim of the project is to identify predictors of recurrence of major depression during a 21-month follow-up after acute treatment. Predictors of remission will include baseline, treatment, and post-treatment measures, detailed below.

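### Combination-phase responders who never remitted are scored for recurrence with the same fixed HDRS-17 cut-off of 14 as remitters, so continuing illness can be recorded as recurrence

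*Protocol article*

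**What the plan says.** **Who enters.** Under Long-term follow-up visits, the eligible patients are "Patients who are remitters at the end of the acute phase, or who are remitters or responders at the end of combination treatment". Monotherapy patients therefore enter only as remitters, while combination patients may enter as remitters or as responders. The Response section confirms this for patients who did not remit on monotherapy "but who meet criteria for response at the end of the combination treatment phase) are offered the option to enter into the long-term follow-up phase".

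**Remission** (Remission section) is an HDRS-17 total below 8 at two ratings: weeks 10 and 12, or weeks 22 and 24 for the combination phase.

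**Response** is a relative criterion: "Response is defined as ≥50% reduction from the baseline HDRS-17 item total score". It rests on a single rating: "Response is determined based on the HDRS-17 item rating at the week 12 and week 24 visits". The baseline appears to be study baseline, because the combination phase is dated from it: "At the end of this 12-week combination treatment period (that is, week 24 from baseline". No maximum score is set for entry as a responder. The Inclusion criteria set minimum HDRS-17 scores (18 at screening, 15 at randomization) and no maximum.

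**Recurrence** (Response section) is any one of four criteria met during follow-up. Criterion 2 is a score of 14 or more at a follow-up visit, repeated the next week. Criterion 3 is "A 17-item HDRS score ≥14 at any follow-up visit, and at which the patient requests an immediate change in treatment for their depressive symptoms". None of the four requires that the patient first remitted, and responders have no separate rule.

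**Use.** The secondary aim is to "identify predictors of recurrence of major depression during a 21-month follow-up after acute treatment".

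**The concern.** One label covers two different events. For a remitter, reaching 14 is a return of illness. For a responder who never remitted, it can be a small fluctuation in residual symptoms or no change at all. The Background itself separates the two states: "Patients who experience a response short of remission are more vulnerable to relapses and recurrences of the disorder".

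The mixing is systematic. By the entry rules, every non-remitted entrant failed monotherapy. If such patients are pooled with remitters in a recurrence model, a predictor can appear to forecast recurrence because it marks residual symptoms or earlier treatment failure. The third fMRI scan shows the risk. It is taken at the end of the 12-week acute phase to predict recurrence, and at that point every patient who later entered through the combination phase was by definition not remitted, while every monotherapy entrant was.

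**Working it through.** The article gives no sample size, power or event count for recurrence, so there is no stated figure to reproduce. The check is integer arithmetic on the definitions, followed by an illustration of size.

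**1. Distance to the cut-off.** The highest week-24 score that still counts as response is floor(baseline / 2). The rise needed is 14 minus the entry score.

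| Baseline HDRS-17 | Highest score counted as response | Rise needed to reach 14 |
|---|---|---|
| 16 | 8 | 6 |
| 18 | 9 | 5 |
| 20 | 10 | 4 |
| 24 | 12 | 2 |
| 26–27 | 13 | 1 |
| 28–29 | 14 | 0 |
| 30 | 15 | already above |

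A remitter enters at 7 or less, so the rise needed is at least 14 − 7 = 7. From baseline 16 upward a responder can enter at 8 or more, and from baseline 28 upward at 14 or more.

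**2. When an unchanged patient is scored.** The entry score alone triggers nothing. A responder who enters at 14 and stays there is scored at the first 3-month visit plus the repeat rating a week later (criterion 2). Criterion 3 also needs a request for a treatment change.

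**3. How many could enter at 14 or more.** The article gives no baseline distribution. Assuming a normal distribution truncated at 15, the share with baseline 28 or more is:
- mean 20, SD 3 to 4: 0.6% to 3.3%
- mean 22, SD 3 to 4: 3.4% to 8.7%
- mean 23, SD 4.9: 18.7%

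Each figure is an upper bound on the share of randomized patients affected, since the patient must also enter as a responder with a score of 14 or more.

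**4. Share of non-remitted responders in follow-up.** Inputs: 400 monotherapy and 240 combination patients and 40% remission (Statistical power/sample size, Table 1), and about 30% more responding without remission (Background). Assumptions: both rates hold in the combination phase, with full uptake and no dropout.
- Monotherapy remitters: 400 × 0.40 = 160
- Combination remitters: 240 × 0.40 = 96
- Combination responders: 240 × 0.30 = 72
- Cohort: 160 + 96 + 72 = 328; responder share 72 / 328 = 22%
- Responder share of 20%: 48 / (256 + 48) = 16%. Of 40%: 96 / (256 + 96) = 27%.

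**5. Share of events, illustration only.** Assume 30% of the 256 remitters recur and the responders' hazard ratio is HR. The responders' event probability is 1 − 0.70^HR.
- Remitter events: 256 × 0.30 = 76.8
- HR 1.5: 1 − 0.70^1.5 = 0.414; 72 × 0.414 = 29.8; 29.8 / (76.8 + 29.8) = 28%
- HR 3: 1 − 0.70^3 = 0.657; 72 × 0.657 = 47.3; 47.3 / (76.8 + 47.3) = 38%

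This gives both groups equal follow-up. Responders have 18 months against 21 for monotherapy remitters, which would lower their share somewhat.

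**The case against.** The strongest reply is that the article never says responders are pooled in the recurrence model. The aim speaks of a 21-month follow-up. The Remission section gives 21 months to monotherapy remitters and 18 to combination remitters, and responders also get 18. The Abstract and Overview attach the 21 months to patients who remit. On this reading the aim concerns monotherapy remitters only, and the choice of analysis set belongs to a statistical analysis plan that is not shown.

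Part of this stands. A reader might infer that a pooled, biased analysis is planned, but Data analyses does not say who enters the recurrence model, so bias in the secondary aim is conditional on pooling. Nor does the Abstract's silence about responders contradict the rest, since it fits the 21/18-month split.

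It does not remove the point. The Response section follows responders until recurrence under the same definition as remitters, and no section restricts the recurrence analysis to remitters or to the 21-month group. How these patients are classified is a rule the article states, and later covariate adjustment would not change the label.

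Two further objections also stand in part. Those already at 14 are probably few. And limiting the set to remitters would still include week-22/24 remitters, all of whom failed monotherapy, so restriction alone does not separate recurrence from monotherapy failure. The fix therefore needs a stratum for entry route.

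**Conclusion.** The entry rule and the recurrence definition do not fit together. A patient who never met the remission definition can be recorded as having a recurrence after a rise of 1 or 2 points or, from baseline 28 upward, after no change. The main weight lies with responders entering at 8 to 13, because the group at 14 or more cannot be sized from the article. Non-remitted responders would be about 22% of the follow-up cohort (16% to 27%) on the assumptions shown. This should be corrected, as it affects the outcome of a stated secondary aim.

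Three stronger readings are not supported:
- That such patients meet recurrence on entry. Criterion 2 needs two follow-up ratings, and criterion 3 needs a treatment request.
- That responders would supply up to 46% of events. That figure, 216 / 472, treats a hazard ratio of 3 as a ratio of event counts. Under the assumptions above the range is 28% to 38%, and the true share is unknown.
- That every responder's recurrence is spurious. Some will worsen genuinely; the definition cannot tell these apart from persistence.

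**What to change.** Make the primary recurrence-predictor analysis set the patients in protocol-defined remission at entry to follow-up (weeks 10 and 12, or 22 and 24). Count time from that entry and use entry route (monotherapy or combination) as a stratum. Report week-24 responders who did not meet the remission definition separately, under an outcome named persistence or worsening. Give a pooled analysis, stratified by entry status (remitter or responder), as a sensitivity analysis only.

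The ratings that define entry status are already collected. Visits, eligibility for follow-up and patient care stay as they are. The cost is a smaller recurrence set: from 328 to 256 in the illustration, about one fifth, with some loss of precision.

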#### Predictors

##### Functional magnetic resonance imaging

Recent developments in image acquisition and data analysis now suggest that resting state studies can be reliably acquired using blood oxygen level-dependent (BOLD) fMRI
[77-79]. Temporally correlated fluctuations in regional activity can be defined using both model-driven (correlations with specific seed regions) and data-driven approaches (that is, independent components analysis or self-organizing maps). These fluctuations agree with the concept of functional connectivity, a descriptive measure of spatio-temporal correlations between spatially distinct regions. Using such methods, decreased low-frequency correlations have been reported in depression
[80-82]. These first results suggest fMRI can identify network abnormalities comparable to those previously identified using PET
[36,83]. Critical to the goal of personalized treatment, resting BOLD fMRI methods can be implemented in scans of individual patients. Resting-state BOLD fMRI scans are acquired prior to initiating treatment and at a fixed, early time-point specific for each treatment. A third fMRI is performed at the completion of the 12 weeks of acute phase treatment, to serve as a predictor of recurrence during maintenance treatment. Pre-treatment scan patterns derived using multivariate analyses and associated with the treatment outcomes will be used to determine whether pretreatment brain patterns can distinguish among outcome groups
[82,84]. A second fMRI scan, acquired early in the treatment course, will be used to assess the likelihood of response to the specific treatment assigned. These analyses will serve as a first step towards defining brain-based subtypes predictive of differential treatment outcome in major depression. The data from these studies will also be entered into more complex algorithms integrating imaging findings with behavioral, environmental, biochemical, and genetic information for individual patients.

